### Recruitment of participants and follow‑up

The data will be extracted from January 1, 2008 to December 31, 2019. A selection period will be defined by the 7 years (January 1, 2008 to December 31, 2014) preceding the index date. It will enable us to identify eligible patients and measure all the variables needed for the calculation of the high dimension propensity score (hdPS). Each participant will be assigned to one of the two study groups on the index date (January 1, 2015), and then followed up to December 31, 2019 (Fig. 1).

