### Study groups and methods of CAD screening

#### Screening group

Individuals who had at least one screening exam (stress electrocardiogram test, stress echocardiography, myocardial scintigraphy coupled with stress test or pharmacological stimulation using adenosine, or coronary CT scan) (Table 2) during the selection period (2008–2015).

**Table 2 Tab2:** Codes used to identify tests to screen coronary artery disease

Tests	Procedure codes
Stress test	DKRP004, EQRP002, EQRM001
Myocardial scintigraphy coupled with stress test or pharmacological stimulation using adenosine	DAQL001, DAQL010, DAQL011, DAQL009
Stress echocardiography	DAQM003, DZQM002, DBQM001
Coronary CT scan	ECQH010
Procedure codes: Codes of the French classification of medical procedure (CCAM)	

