#### No-screening group

Participants who never experienced a screening exam as described above during the selection period (2008–2015), except resting electrocardiogram.

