### Statistical analysis plan

The data will be analysed by the biostatistician of the “Clinical Epidemiology Unit” of the University Hospital of Bordeaux (USMR). Analyses will be performed using SAS® software, version 9.4 or later (SAS Institute, Cary, NC, USA, http://www.sas.com) and all tests will be performed at the first-order error risk α = 5%. The flow-chart (CONSORT), as well as the characteristics of patients at inclusion (eligibility criteria, epidemiological, clinical, biological characteristics and treatment use) will be presented. Confounding factors will be taken into account through a hdPS score that will involve around 500 variables, according to the Bross formula [26]. A principal component analysis will then allow us to reduce the dimensionality to 30 components, and the goodness of fit of this hdPS score will be estimated by a graphical comparison of the score distribution and by standardized mean differences between the two study groups [27]. Comparisons between the two groups will be carried out with and without adjustment for the hdPS score, and the hypotheses of the different regression models chosen, will be systematically verified.

Regarding the analysis of the primary endpoint, a gross estimate of the incremental cost per life-year gained at 5 years will be conducted. The confidence interval (CI) of this incremental cost-effectiveness ratio will be estimated by boostrap (5000 iterations). The analysis will be performed as Intent to Treat. To investigate a possible relationship between the frequency of screening and survival, we will define four different subgroups: screening conducted at least once a year, less than once a year (and at least once every two years), less than once every two years (and at least once every three years), and only once during the follow-up period.

A cost-consequence analysis will be performed linking results of all direct costs (observed during the following period) and results on major cardiovascular events. A budget impact analysis will be conducted to determine the public expenses of the spread of a systematic screening for silent ischemic CAD.

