### Cost-effectiveness of routine CAD screening in patients with diabetes

Systematic CAD screening strategy leads to more invasive examination, especially coronary angiography, which is associated with increased risk of complications [11, 12]. Routine CAD screening encourages also revascularizations and intensification of pharmacological treatments, despite uncertainties in terms of related benefits. In the FACTOR-64 study, CAD screening was not associated with a significant reduction in major cardiovascular events despite intensive pharmacological control of cardiovascular risk factors (and some coronary revascularizations) in patients with a positive screening test, while individuals assigned to control group and those with a negative screening test had only conventional cardiovascular treatment goals [13]. Furthermore, BARDOT (Basel Asymptomatic high-Risk Diabetics' Outcome Trial) study showed that combined medical therapy and invasive strategy (coronary angiography followed or not by revascularization) for silent CAD, compared with medical treatment alone, was associated with reduced scintigraphic CAD progression, but no significant difference was observed in terms of hard clinical events in high risk T2DM patients [28]. Therefore, to avoid unjustified health expenses and misuse of collective resources associated with routine CAD screening, we conduct the SCADIAB study to assess the cost-effectiveness of this strategy in people with T2DM and a very high cardiovascular risk.

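### The hdPS covariates are measured over the same 2008–2014 window as the exposure, with no cut-off at the first exam, so the adjusted comparisons can remove part of the effect of screening

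*Protocol article*

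**What the plan says.** Under *Recruitment of participants and follow-up*, the protocol article states: "A selection period will be defined by the 7 years (January 1, 2008 to December 31, 2014) preceding the index date". The same paragraph says this period will serve to identify eligible patients and to "measure all the variables needed for the calculation of the high dimension propensity score (hdPS". It then fixes a common start: "Each participant will be assigned to one of the two study groups on the index date (January 1, 2015").

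Exposure is read from the same period. The *Screening group* has at least one listed exam "during the selection period (2008–2015"). The comparator is defined as: "Participants who never experienced a screening exam as described above during the selection period (2008–2015), except resting electrocardiogram".

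On the score, the *Statistical analysis plan* section states: "Confounding factors will be taken into account through a hdPS score that will involve around 500 variables, according to the Bross formula". These variables are then reduced to 30 principal components. Fit is judged by comparing score distributions and by standardized mean differences. Comparisons are made with and without the score, and the Cox hazard ratios are adjusted for it.

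On what screening sets in motion, the Discussion states: "Routine CAD screening encourages also revascularizations and intensification of pharmacological treatments". It adds that screening leads to more invasive examination, coronary angiography above all. The *Background* says much the same.

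**The concern.** A confounder has to precede the exposure. Here covariates need only precede 1 January 2015, which is the date on which patients are sorted into groups. The exam itself may lie up to seven years earlier. Prescriptions, visits and angiographies recorded between the exam and the index date may be results of the exam, and they are the routes by which screening could change survival and cost.

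Three planned features make the problem harder to see or undo:

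- The Bross formula ranks codes by their association with exposure and outcome. Care that follows an exam is a natural candidate on both counts.
- The 30 components mix information from before and after the exam, so downstream care cannot easily be taken out later.
- The planned checks reward balance. A score that balances a consequence of the exam looks like a success.

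The article calls its analysis intention-to-treat, which points to the total effect of the strategy. Adjusting for care that the strategy produced estimates something else. A spurious null would also be easy to believe, because it would agree with the earlier trials in Table 1, and the *Conclusions* say the findings will guide recommendations.

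**Working it through.** **1. The windows by date.**

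| Item | Window | Section |
|---|---|---|
| hdPS covariates | 1 Jan 2008 to 31 Dec 2014 | Recruitment of participants and follow-up |
| Exposure | Selection period, end year printed as 2015 | Screening group; No-screening group |
| Group assignment and start of follow-up | 1 Jan 2015 | Recruitment of participants and follow-up |

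The covariate window lies wholly inside the exposure window. The two end years (31 December 2014 and 2015) need reconciling, but the overlap holds under either.

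**2. Post-exam time that can enter the score.** This is 31 December 2014 minus the exam date:

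- exam at the start of 2008: about 7 years;
- exam during 2009: 5 to 6 years;
- exam during 2014: 0 to 1 year.

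Unscreened patients have no exam date, so all their covariate time is unexposed.

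**3. The plan's own figure.** The article gives no figure for this bias. Its only sample-size figure reproduces: 2,400,000 × 0.38 × 0.10 = 91,200, against at least 90,000 stated. That number offers no protection, because this bias does not shrink as the sample grows.

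**4. Illustrative size.** The document gives no effect sizes, so every input here is an assumption. Each scenario used 5 runs of 400,000 patients.

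- Baseline confounder C: standard normal.
- Screening S: logit P(S) = 0.5 × C.
- Care before the exam, M0: logit P(M0) = −1 + 0.5 × C.
- Care by the index date, M: present if M0 is present, or if the patient was screened and the exam started it (probability 0.35).
- True total effect of screening: −2.0 points on 5-year risk, of which a share s runs through M.
- Risk = 0.20 + 0.03 × C (C truncated at ±3) + (1 − s)(−0.02) × S + [s(−0.02) / (0.35 × (1 − P(M0)))] × M.

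Risk differences were estimated by inverse-probability weighting. One propensity score used C and M0 (care before the exam); the other used C and M (care up to the index date). Share lost = 1 − (second estimate / first estimate).

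| Share s through post-exam care | Covariates before exam | Covariates to index date | Share lost |
|---|---|---|---|
| 0% | −2.08 points | −2.08 points | 0% |
| 25% | −1.98 | −1.49 | 25% |
| 50% | −1.97 | −1.00 | 50% |
| 75% | −2.02 | −0.49 | 76% |
| 100% | −2.01 | 0.00 | 100% |

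The pre-exam score recovers about −2.0 throughout. Up to simulation error, the full-window score loses the mediated share.

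**The case against.** **The score's content is inferred.** The article does not list the roughly 500 variables, nor does it say that every variable pools all seven years. Candidate lists and barred codes are commonly left to a fuller document, and Fig. 1 is not available. This stands as a limit: the text allows post-exam care into the score but does not say that any given code will be there. It does not remove the point, because the article does fix the covariate window, and fixes it without reference to the exam.

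**The size is built in.** A reader might infer that adjustment removes essentially the whole effect. That holds only if the whole effect is assumed to run through the adjusted care. The simulation also enters one mediator directly, whereas 30 components may dilute single codes.

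**Near-violation of positivity.** A reader might also infer that angiography after a stress test all but determines exposure. The document gives no figure for how common angiography is in either group, so this is unsupported.

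**Revascularization and prior treatment.** *Exclusion criteria* removes patients with a history of coronary revascularization or angina. If that is applied up to the index date, revascularization cannot enter the score; excluding patients on a possible result of the exam is a separate question. Hypertension and hypercholesterolemia can qualify patients through drug deliveries, so many may already be treated, leaving less room for drug starts prompted by the exam. Angiography, visits and further drug intensification remain open.

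**Reach to the primary endpoint.** The *Statistical analysis plan* section calls the incremental cost-effectiveness ratio a gross estimate, while the Abstract says analyses will be adjusted for the score. It cannot be concluded that the primary result is affected.

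**Conclusion.** The point holds for the hdPS-adjusted comparisons, including the adjusted Cox hazard ratios. The covariate window coincides with the period in which exposure is ascertained, nothing stops measurement at the first exam, and the article itself attributes angiography and drug intensification to screening. Whether the primary ratio is affected is unclear on the text.

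The expected direction is generally toward no effect. This assumes that the mediated part has the same sign as the total effect. It also assumes that post-exam care and outcome share no strong unmeasured cause; if they did, the estimate could move either way. The size depends on the share of the effect running through post-exam care that the score captures. It ranges from 0% to 100% in the illustration and cannot be computed from the document. The document supports neither near-total loss nor a positivity failure.

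**What to change.** - Measure hdPS covariates only up to the day before the first qualifying exam in screened patients. In unscreened patients, measure them up to a pseudo-date drawn to match the calendar distribution of exam dates. Use the same look-back on both sides of each matched date.
- Exclude the qualifying exams themselves and post-exam coronary angiography from the candidate covariates.
- Keep the full-window score only as a sensitivity analysis.
- State whether the primary cost-effectiveness ratio is adjusted, and print one end date for the selection period.

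**Cost.** No new data are needed, but this is more than a change of wording: each patient needs a cut-off date and the score must be built on it. Data begin on 1 January 2008, so a 12-month look-back is impossible for exams in 2008, and a 24-month look-back is impossible for exams in 2008 and 2009. Those exams need a shorter common look-back or exclusion from the adjusted analysis. Changes in health between the exam and 1 January 2015 would also go unadjusted unless follow-up is started at the matched date, which would be a larger change of design.

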#### Exclusion criteria

One of the following:The presence of CAD (defined as a history of acute coronary syndrome, coronary revascularization, angina pectoris, or unstable angina).Any visit to an emergency department for chest pain resulting for admission to a cardiac intensive care unit.

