### Screening for silent CAD and risk of major cardiovascular events

Previous RCTs demonstrated no clinical benefit associated with routine CAD screening in asymptomatic T2DM patients, but population with a high cardiovascular burden and any organ vascular damage has not been investigated [11–14]. Also, the observed incidence of outcomes was much lower than expected in published RCTs evaluating the interest of routine CAD screening in individuals with T2DM (Table 1). The conduction of a new prospective RCT will be too expensive, time-consuming with difficulties for recruiting asymptomatic participants with a very high cardiovascular risk. Indeed, the DYNAMIT (Do You Need to Assess Myocardial Ischemia in Type-2 diabetes) study was stopped prematurely due to difficulties in recruitment of participants and a low incidence of cardiovascular events [12]. DYNAMIT included only one-fifth (631/3000) of the originally planned enrolment to detect a 20% relative risk reduction (RRR) in the primary endpoint (a composite of all-cause death, non-fatal myocardial infarction, non-fatal stroke, or heart failure requiring hospitalization or visit to emergency department) in people with T2DM at a high cardiovascular risk (aged 55 to 75 years with at least 2 other cardiovascular risk factors). A recent meta-analysis estimated that a large number of participants would be needed to demonstrate a potential benefit of the systematic CAD screening strategy to reduce the incidence of major cardiovascular events [15]. The optimal sample size for 20% RRR of major cardiac events should be 29,763 participants (19,548 for all-cause death). Therefore, a retrospective RWE study seems to be an appropriate approach to evaluate the long-term cost-effectiveness of systematic CAD screening strategy in T2DM subjects at a very high cardiovascular risk without known history of CAD. Of note, among 3.7 million people with diabetes in France, we estimate that at least 90,000 individuals will be eligible for our study in the SNDS database.

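### CAD found by screening before 1 January 2015 counts as an exclusion, so the screening arm loses screen-positives before follow-up starts

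*Protocol article*

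**What the plan says.** The Recruitment section of the Protocol article dates the windows: "A selection period will be defined by the 7 years (January 1, 2008 to December 31, 2014) preceding the index date". The same window serves eligibility and covariates: "It will enable us to identify eligible patients and measure all the variables needed for the calculation of the high dimension propensity score (hdPS". Assignment comes at its end: "Each participant will be assigned to one of the two study groups on the index date (January 1, 2015"; participants are assigned "and then followed up to December 31, 2019".

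The Screening group consists of "Individuals who had at least one screening exam" in the selection period. The No-screening group consists of "Participants who never experienced a screening exam as described above during the selection period". (Both group definitions label the period 2008–2015, whereas the Recruitment section ends it on 31 December 2014. I use the dated statement; the two should be reconciled.)

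The first exclusion criterion is "The presence of CAD (defined as a history of acute coronary syndrome, coronary revascularization, angina pectoris, or unstable angina". It carries no date. The Discussion describes the target as "T2DM subjects at a very high cardiovascular risk without known history of CAD".

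The Background and the cost-effectiveness part of the Discussion both say that screening leads on to revascularization. The Statistical analysis plan section labels the primary analysis as intention to treat. In its cost-consequence paragraph it describes direct costs as those seen during follow-up.

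**The concern.** Exposure, eligibility and the start of follow-up fall at different times. The exam may date from 2010, eligibility is settled over the whole selection period, and the clock starts in 2015. Anything an exam causes between those dates can decide whether the patient is in the study at all. By the article's own account, one consequence of screening is revascularization, which is an excluding event.

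The primary endpoint is the incremental cost per life-year over 5 years. Any benefit, harm or cost of screening runs largely through patients in whom it finds disease. If a share of them leave the screening arm before follow-up, both terms of the ratio and every hazard ratio are conditioned on a result of the exposure. An intention-to-treat label does not fit a cohort selected that way.

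**Working it through.** **The article's own figure.** The Sample size section gives 2.4 million people with T2DM free of CAD, 38% with at least two risk factors, and more than 10% with vascular disease: 2,400,000 × 0.38 × 0.10 = 91,200. This agrees with the stated minimum of 90,000. It is a feasibility count, and the point below does not depend on it.

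**Following one patient through the rules.** She is eligible and is tested in 2010. The test is positive and she is revascularized in 2011. On 1 January 2015 she has an exam in the selection period, so she is exposed, and a history of coronary revascularization, so she is excluded. An identical patient who is never tested, and whose disease stays silent, enters the no-screening arm. A third patient, tested positive but managed medically with no angina code, stays in the screening arm. The arm is thus depleted of positives, not emptied of them.

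**Size of this one mechanism if screening has no effect.** The article gives none of these inputs; all are assumed.
- p: share of patients whose test is, or would be, positive
- r: outcome risk ratio, positive versus negative
- f: share of screened positives with an excluding CAD code before 2015
- g: share of equivalent unscreened patients with such a code before 2015

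Risk relative to a test-negative patient, when a share x of positives is removed:

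R(x) = [(1−p) + p(1−x)r] / [(1−p) + p(1−x)]

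The apparent relative risk is R(f)/R(g).

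- p = 0.20, f = 0.50, g = 0, r = 2: R(f) = (0.8 + 0.2)/0.9 = 1.111; R(g) = 1.2; ratio **0.93**.
- Same with r = 3: (1.1/0.9)/1.4 = 0.87. With r = 4: (1.2/0.9)/1.6 = 0.83.
- p = 0.20, f = 0.50, g = 0.25, r = 2: R(g) = (0.8 + 0.3)/0.95 = 1.158; 1.111/1.158 = **0.96**.
- r = 1.5 with g = 0: (0.95/0.9)/1.1 = 0.96. With g = 0.25: 1.056/1.079 = 0.98.
- Extremes over p = 10–30%, f = 25–75%, r = 2–4, g = 0: (1.05/0.975)/1.1 = 0.98 and (1.0/0.775)/1.9 = 0.68.
- If g = f the ratio is 1. Only the difference in exclusion between the arms matters.

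**Cross-check in life-years.** Assume a death hazard of 3% a year without CAD and 6% with silent CAD, 20% prevalence, 10% of silent CAD surfacing before 2015 in both arms, and half of the remaining screened cases excluded. The CAD share left is 0.2 × 0.45/0.89 = 0.101 in the screening arm and 0.18/0.98 = 0.184 in the other. Five-year mortality is 15.1% versus 16.1%, a cumulative-hazard ratio of 0.93. Mean survival over 5 years is (1 − e^(−5h))/h, that is 4.643 years without CAD and 4.320 with it. The spurious gain is 0.323 × (0.184 − 0.101) = 0.027 life-years per person. Over prevalence 10–30%, exclusion 25–75% and relative hazard 2–3, the hazard ratio runs from 0.98 to 0.77 and the gain from 0.007 to 0.117. With the CAD exclusion applied only before time zero, the same model gives 1.00 and 0.

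**Deaths before the index date.** At an assumed 2–5% a year, 1 − e^(−0.14) = 13% to 1 − e^(−0.35) = 30% of a 2008 cohort die before 2015. They leave both arms, so this loss has no fixed direction.

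**Adjustment.** The hdPS balances the patients who remain. It cannot bring back those removed, and its covariates come from the exposure window, so some may follow the exam.

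**Costs.** If direct costs are those of follow-up, the pre-2015 exam and the work-up it triggered appear to lie outside the ICER. The wording stands in the cost-consequence paragraph; its extension to the ICER is inferred from the 5-year horizon.

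**The case against.** The CAD exclusion has no date and the design figure is not visible, so applying it up to 1 January 2015 is an inference. It is the natural one: eligibility is identified over the whole selection period, the target is patients without known CAD, and no wording limits the exclusion to CAD before the exam.

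A reader might infer that the screening arm consists of screen-negative survivors. The criteria do not support that, because a positive test without an excluding code is not itself an exclusion.

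A reader might also infer that screening will be made to look protective. That treats one mechanism as the net result. Unscreened patients with manifest CAD before 2015 are removed too, which offsets part of the effect. Early deaths leave both arms, and confounding by indication may act in the opposite direction. All of this stands.

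Nor is the study void. CAD first found by repeat exams in 2015–2019 stays in the screening arm, and the article's question concerns repeated routine screening. The contrast is biased rather than empty.

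The inputs are also open to challenge. A risk ratio of 2 to 4 for death may be high in patients who already have kidney, cerebral or limb vascular disease. The figures are therefore illustrative only. What remains unanswered is that the article describes nothing that keeps screen-detected CAD in the screening arm. The safeguards in its Strengths and limitations section (pre-specified criteria, the 7-year selection period, the hdPS) do not do so.

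**Conclusion.** The concern holds in this form: followed as written, and with the exclusion read up to the index date, the plan selectively removes from the screening arm patients whose CAD was found and coded after their exam. Under no true effect this mechanism alone gives a relative risk of about 0.93 in the central illustration and 0.96 with a 25% offset in unscreened patients. Without that offset the range is about 0.98 to 0.68. Every input is assumed. The net direction, once other selection and confounding by indication are added, is uncertain. A cohort of some 90,000 does not help, since a large sample shrinks sampling error and leaves this bias where it is. The flaw reaches the primary ICER and all hazard ratios, and hdPS adjustment cannot repair it, so it should be corrected before the analysis begins.

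**What to change.** Replace the single index date with sequential emulated trials on the data already requested:
- Set a fixed look-back for prior CAD, prior exams and hdPS covariates, for example 2 to 3 years. Extraction starts on 1 January 2008, so time zeros would run monthly or quarterly from 2010 or 2011 to December 2014, each with 5 years of follow-up by 31 December 2019.
- At each time zero, take patients who meet the inclusion criteria and have no prior CAD. Classify them by whether an exam occurs in that interval. Keep the interval short, because this classification looks forward by its length.
- Apply the CAD exclusion and measure hdPS covariates only before time zero. CAD found by the exam then stays in the screening arm.
- Count life-years and costs, including the exam and its work-up, for 5 years from time zero.
- Analyse as assigned and report later screening in controls. Add a sensitivity analysis that censors controls at later screening, with weights. Bootstrap by patient, because one person can enter several trials.

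The cost is protocol wording and programming; the article says that analyses had not yet started. The downsides are a look-back shorter than 7 years, diabetes duration read from the coverage start date for early time zeros, and dilution from controls screened later.

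If the 2015 index date is kept, the conclusion should be confined to patients alive and CAD-free on 1 January 2015, with versus without a past exam. It should not be presented as the effect or cost-effectiveness of screening.
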